### Study design

This study is a randomized, parallel-group controlled trial to evaluate the effectiveness of a Baduanjin exercise intervention on the physical fitness of college students. A total of 120 eligible college students from the Shanghai University of Medicine and Health Sciences (SUMHS) will be recruited and randomly allocated to either the Baduanjin exercise group or the control group at a ratio of 1:1. Participants in the Baduanjin exercise group will receive a 12-week supervised Baduanjin exercise training intervention with a frequency of 1 h each day and 4 days per week, while those in the control group will not receive any specific exercise intervention and will be informed to maintain their original lifestyle for 12 weeks. Primary and secondary outcomes will be measured at baseline and after the 12-week intervention period. The participant flow for this trial is presented in Fig. 1. The present protocol follows the Standard Protocol Items: Recommendations for Interventional Trials (SPIRIT) guidelines and fulfills the SPIRIT checklist (see Additional file 1).

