### Sample size calculation

The primary outcome of this trial involves global health-related physical fitness ability changes which are assessed using composite points of health-related physical fitness. According to study data [34], the mean and standard deviation of a composite point in the health-related physical fitness of college students were measured as 55 points and 12.5 points, respectively. A sample size of 100 will have 80% power to detect a difference in a composite score of health-related physical fitness of 5.0% and an α of 0.05 for a two-sided significance level. Assuming a maximum loss to follow-up of 20%, a total of 120 subjects was necessary.

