### Statistical analysis

Analysis of data in this trial will be performed by a statistician who is not involved in the trial. In descriptive analysis of the sample, continuous variables will be expressed by using the mean and standard deviation for normal distributions, and the median and interquartile range for non-normal distributions. Normality will be tested using the Kolmogorov–Smirnov test. Appropriate transformations will be applied in cases of non-normal distribution. Categorical variables will be expressed as proportions with their standard error.

Baseline characteristics between groups will be compared using the *t* test or Mann–Whitney test for continuous variables and Pearson’s χ-squared or Fisher’s exact test for categorical variables. If incomparability appears, the inequality factors will be treated as confounding variables in the final efficacy analysis.

For comparison of primary and secondary outcomes between groups, a *t* test or non-parametric tests will be used for continuous data, and Pearson’s χ-squared or Fisher’s exact test for categorical data at baseline and after intervention; the between-group differences (treatment effects) will be analyzed by using mixed linear models with restricted maximum likelihood using the group-by-time interaction terms. Analysis of the outcomes will be performed on the basis of the intention-to-treat (ITT) population. All participants who have been randomized will be included in the final analysis irrespective of compliance or withdrawal from the program. Full information maximum likelihood estimation will be employed for missing data.

AEs will be listed and analyzed using a χ-squared test or Fisher’s exact test. Severe AEs will be listed and described in detail.

All data will be analyzed with SPSS 21.0 (IBM, Chicago, IL, USA) software packages. Statistical significance is defined as a two-sided *P* value of < 0.05.

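### The primary composite gets two between-group significance tests at 0.05, neither labelled descriptive, and the week-12 t or rank test cannot meet the all-randomised rule

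*Protocol article*

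**What the plan says.** In the Statistical analysis section, one sentence sets out two between-group analyses of the primary and secondary outcomes. In its first half, a t "test or non-parametric tests will be used for continuous data", applied at baseline and again after the intervention. In its second half, the treatment effect is analysed by a mixed linear model, fitted by restricted maximum likelihood, through the group-by-time interaction. The Abstract names only mixed linear models for the effect of the exercise.

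The population rule follows directly: "All participants who have been randomized will be included in the final analysis irrespective of compliance or withdrawal from the program". Missing data are to be handled by full information maximum likelihood. The section ends with one threshold for all tests: "Statistical significance is defined as a two-sided" P value below 0.05. The Sample size calculation uses the same level, "an α of 0.05 for a two-sided significance level".

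The paragraph on describing the sample calls for a Kolmogorov–Smirnov test of normality and adds: "Appropriate transformations will be applied in cases of non-normal distribution".

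**The concern.** With one follow-up visit, a week-12 comparison and a group-by-time interaction address the same question with different statistics. The first ignores baseline and the second subtracts it. They can disagree, and the plan does not say in terms which P value is confirmatory. A final report could show both, and a reader could not use this section to rule out a claim resting on the more favourable one.

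The two also differ in whom they use. A two-sample t or rank test needs a week-12 value from each student it counts, whereas the mixed model can keep a student who has only a baseline value. So one of the two prescribed analyses does not fit the population and missing-data rules stated just after it.

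**Working it through.** **Inputs from the protocol.** Two-sided level 0.05 (Sample size calculation and Statistical analysis); two visits, baseline and week 12 (Outcome assessment); 1:1 allocation (Study design); 120 students and a maximum loss of 20% (Sample size calculation).

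**Assumed inputs.** The protocol does not give the correlation ρ between baseline and week-12 composite scores, so a range of 0.3 to 0.9 is used. Variances are taken as equal at the two visits and data as complete.

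**The plan's own figure.** The protocol states 0.05 and gives no family-wise error. If the interaction is the only deciding test, the error is 0.05, as stated.

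**Correlation of the two tests.** With two visits and complete data, the interaction is the difference between arms in mean change. Let V be the variance of the between-arm difference in means at either visit.

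- Variance of the week-12 difference: V
- Variance of the difference in change: 2V(1 − ρ)
- Covariance of the two: V(1 − ρ)
- Correlation: r = V(1 − ρ) / √[V × 2V(1 − ρ)] = √[(1 − ρ)/2]

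**Chance that at least one is significant under no effect.** This is 1 − P(|Z1| < 1.96 and |Z2| < 1.96) for a bivariate normal pair with correlation r.

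| ρ | r | P(either significant) |
|---|---|---|
| 0.3 | 0.592 | 0.0878 |
| 0.5 | 0.500 | 0.0907 |
| 0.7 | 0.387 | 0.0935 |
| 0.8 | 0.316 | 0.0949 |
| 0.9 | 0.224 | 0.0962 |

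Two independent tests would give 1 − 0.95² = 0.0975, so the range lies just below that value. A simulation of t tests on week-12 scores and on change scores, with 50 per arm, gave 0.089, 0.094 and 0.094 at ρ = 0.5, 0.7 and 0.9. Each test alone rejected in about 5% of runs.

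**Students left out of the week-12 test.** At the maximum loss this is 0.20 × 120 = 24. The plan's own step from 100 to 120 leaves room for 120 − 100 = 20. Baseline is measured before allocation (Randomization, allocation, and blinding), so these students should have a baseline score that a mixed model can use and a week-12 test cannot.

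**Effect of adjusting for baseline.** Relative to the change-score interaction, the variance of the baseline-adjusted week-12 difference is (1 − ρ²) / [2(1 − ρ)] = (1 + ρ)/2, which is 0.65 at ρ = 0.3 and 0.95 at ρ = 0.9. Adjustment alone does not remove the ambiguity. If an unadjusted week-12 P value stayed as an alternative route to a claim, the same calculation with r = √(1 − ρ²) gives 0.064 at ρ = 0.3 and 0.092 at ρ = 0.9.

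**The case against.** The strongest reply is that the plan already chooses. The Statistical analysis section attaches the treatment effect to the mixed model, and the Abstract names nothing else. Nowhere is a significant t or rank test said to count as success. This stands: a reader might infer that the plan carries a 9% error rate, and the documents do not support that as a property of the plan.

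A reader might also infer that a completers-only analysis is prescribed. The text says no such thing and puts outcome analyses on an intention-to-treat basis. The omission follows from how a two-sample test works when no imputation is stated, and it does not affect the analysis named for the treatment effect.

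A third tempting reading is that the normality test can move the primary effect off the points scale. The transformation sentence sits in the paragraph on describing the sample, and nothing applies it to the mixed model. It only needs its scope stated. Nor can the scale argument lean on a five-point target, because the Sample size calculation states the difference as 5.0% and does not say whether that means points.

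The baseline tests open no route to a false efficacy claim. In randomised arms any baseline difference is due to chance, so they are merely uninformative.

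Finally, labelling supporting tests can be left to an analysis plan that is not shown. That would answer an omission. Here the article itself prescribes both analyses in one sentence under one threshold, next to a population rule that one of them cannot follow.

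**Conclusion.** The point holds in a limited form. Two inferential comparisons of the primary composite are planned at an undivided 0.05, and the first is not marked as descriptive. The type I error is 5% if the mixed model alone decides, as the wording suggests. It would be about 8.8% to 9.6% if either test could support a claim, given ρ between 0.3 and 0.9, equal variances and complete data. Separately, without imputation the week-12 t or rank test would leave out up to 24 of 120 students at the assumed maximum loss, against the all-randomised rule. The change is worth making because it bears on how the primary result is read. It does not invalidate the mixed-model analysis.

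**What to change.** State that the sole primary test is the week-12 group difference in the untransformed composite from the mixed model, adjusted for baseline or with the baseline means constrained equal, fitted by restricted maximum likelihood and including all randomised students. The constrained form suits the population rule better: it treats both visits as responses, so students with only a baseline value stay in the model. Entering baseline as a covariate for a single follow-up value would drop them.

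Present baseline and week-12 summaries by group without P values. State that the normality test and transformations apply to descriptive summaries only. A bootstrap interval as a check on model residuals is optional. Date the change before outcome data are analysed.

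The cost is a small change to the stated interaction model and fewer P values in the report. No new data are needed, because baseline is already collected.

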#### Outcome assessment

Outcome measurement of participants will be performed at the campus gymnasium by physical education teachers who do not participate in the implementation of this trial. Primary and secondary outcomes will be assessed at baseline and after the 12-week intervention period.

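### Taking the treatment effect from a two-time-point group-by-time interaction is valid but, on its usual reading, gives up precision that a common baseline mean would recover at no data cost

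*Protocol article*

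**What the plan says.** The Protocol article measures outcomes twice: "Primary and secondary outcomes will be assessed at baseline and after the 12-week intervention period" (Outcome assessment). The section on randomization places the baseline assessment before students learn their allocation.

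The effect estimate is set in Statistical analysis: "the between-group differences (treatment effects) will be analyzed by using mixed linear models with restricted maximum likelihood using the group-by-time interaction terms". The section does not list the other model terms. It does not say whether each arm has its own baseline mean or both share one, and it does not name the baseline value of the outcome as a covariate. Adjustment is foreseen only for factors found unequal in baseline tests. The same section includes every randomised student and handles missing data by full-information likelihood.

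The sample size section describes the primary outcome as "global health-related physical fitness ability changes which are assessed using composite points of health-related physical fitness". It gives a mean and SD that "were measured as 55 points and 12.5 points, respectively", a single-occasion SD. It gives neither an SD of change nor a baseline to week-12 correlation.

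**The concern.** A model with group, time and group-by-time terms normally estimates a separate baseline mean in each arm. Before allocation is known, two randomised groups differ at baseline only by chance, so estimating that difference and subtracting it in full adds noise. Replacing full subtraction by a regression on baseline, or by one shared baseline mean, removes part of the noise.

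At stake is the width of the primary confidence interval. The baseline composite is to be measured on every student before allocation is disclosed, and recruitment has closed (Trial status), so the analysis is one of the few places where precision can still be gained. Adjusting only when a baseline test is significant does not achieve this: the gain comes from the correlation between baseline and week 12, not from whether an imbalance crosses a significance threshold.

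**Working it through.** **Inputs.** SD 12.5 (Sample size calculation), assumed equal at both occasions. Allocation 1:1 (Study design), so 60 per arm from 120. Loss of 20% ("Assuming a maximum loss to follow-up of 20%, a total of 120 subjects was necessary"), so 60 × 0.8 = 48 per arm with week-12 data. Two-sided α 0.05. The difference is given as 5.0 with a percent sign: it is read here as 5 points on the 100-point scale, but 5% of the mean of 55 is 2.75 points. The baseline to week-12 correlation ρ is not in the document and is varied from 0.5 to 0.9.

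**The plan's own figure.** The section states: "A sample size of 100 will have 80% power to detect a difference in a composite score of health-related physical fitness of 5.0" (percent sign follows). Per arm, n = 2 × (1.960 + 0.842)² × 12.5² / 5² = 98.1, so 99 per arm or 198 in total. With 50 per arm, the power for 5 points is 52%, and the difference detectable with 80% power is 2.802 × 12.5 × √(2/50) = 7.0 points. The stated total of 100 therefore does not follow from the single-occasion SD. That is a separate matter; here it shows only that no correlation can be recovered from the calculation.

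**Complete data.** With separate baseline means, the interaction is the difference in mean change, with variance 2 × SD² × 2(1−ρ)/n. With baseline adjustment the variance is 2 × SD² × (1−ρ²)/n. The ratio is (1+ρ)/2, which is below 1 for every ρ below 1. In one simulated data set (50 per arm, ρ = 0.7), the REML interaction and the change-score analysis gave the same estimate and standard error (6.105, SE 1.765). ANCOVA gave SE 1.710, and a mixed model with a common baseline mean gave SE 1.636.

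**With week-12 data missing.** Likelihood estimation keeps the 12 baseline-only students per arm. Assuming missingness at random and treating the covariance as known:

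- interaction, separate baseline means: 2 × SD² × [(1−ρ²)/48 + (1−ρ)²/60]
- common baseline mean: 2 × SD² × (1−ρ²)/48

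Example at ρ = 0.5: (1−ρ²)/48 = 0.015625 and (1−ρ)²/60 = 0.004167. The variances are 2 × 156.25 × 0.019792 = 6.185 (SE 2.487) and 2 × 156.25 × 0.015625 = 4.883 (SE 2.210). The saving is 0.004167/0.019792 = 21%.

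Power for a 5-point difference (noncentral t, 94 and 93 degrees of freedom):

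| Assumed ρ | Interaction | Baseline-adjusted | Variance saving |
|---|---|---|---|
| 0.5 | 51% | 61% | 21% |
| 0.6 | 60% | 68% | 17% |
| 0.7 | 72% | 78% | 12% |
| 0.8 | 87% | 90% | 8% |
| 0.9 | 99.2% | 99.4% | 4% |

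If the difference is 2.75 points, the same formulas give 19% against 23% at ρ = 0.5, 29% against 32% at 0.7, and 67% against 69% at 0.9. The variance savings do not change.

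**The case against.** The strongest reply is that the article never says the baseline means are free. A model with a time effect and a group-by-time term, but no group main effect, has a common baseline mean and also uses the interaction term, so the quoted sentence is compatible with the efficient model. A condensed article may leave the exact terms to an analysis plan that is not shown. This stands: separate means are the usual reading, not the stated one, and the point partly asks for clarification.

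Second, a reader might infer that with 48 completers per arm the interaction is a pure change score, so that the saving is 25%, 20%, 15% and 10% at ρ of 0.5, 0.6, 0.7 and 0.8. The documents do not support this. Those figures use the complete-data variance, whereas the plan keeps baseline-only students through the likelihood; the savings then fall to 21%, 17%, 12% and 8%.

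Third, the plan already allows adjustment for unequal baseline factors. That is true, but it is conditional on the data and would drop a prognostic baseline value whenever its test was not significant. It does not replace a pre-specified adjustment.

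Fourth, the planned analysis is valid. This also stands in full.

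**Conclusion.** The point holds as one of efficiency. On its usual reading, the planned interaction is less precise than a model that uses the shared pre-allocation baseline. For a 5-point difference the loss is about 10 power points at ρ = 0.5, 6 at 0.7, 3 at 0.8 and almost none at 0.9. These figures assume 48 of 60 completing per arm, missingness at random, equal SDs of 12.5 and a correlation that the document does not give.

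Two stronger conclusions might be drawn and are not supported. One is that the interaction estimate is biased or its test invalid; under randomisation neither is so. The other is that this choice explains, or its correction cures, the mismatch in the sample size calculation. At ρ = 0.5 baseline adjustment still gives only 61% power for 5 points, while at ρ = 0.8 both analyses exceed 80%. The mismatch needs its own answer.

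**What to change.** Before unblinding, state that the primary analysis is a mixed model with both occasions as outcomes, one baseline mean common to the two arms, a time effect, a group effect at week 12 and an unstructured covariance. The primary result is the week-12 difference in composite points with its 95% confidence interval. Say that this model is used whatever the baseline significance tests show, and apply it to the continuous secondary outcomes as well.

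ANCOVA of the week-12 value on baseline has similar precision, but without imputation it leaves out students who lack week-12 data, whom the intention-to-treat statement includes. It therefore belongs among the sensitivity analyses and is not a full substitute.

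The cost is a sentence or two of analysis wording. The model can be fitted with the mixed-model procedure of the planned SPSS software and needs no new data. If the intended model already has a common baseline mean, saying so settles the main point; only the rule that makes adjustment depend on baseline tests would then need clarifying.

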### Ethics

The conduct of the study will conform to the principles of the Declaration of Helsinki and relevant ethical guidelines covering informed consent, confidentiality, and data storage. Ethical approval has been obtained from the Ethics Committee of Shanghai University of Medicine and Health Sciences (approval number 2017ZGH). All participants will be fully informed about the trial and will sign the informed consent form prior to participation.

### Monitoring

Due to the low-risk nature of the aerobic exercise intervention, we do not anticipate any potential harms. Therefore, there will be no Data Monitoring Committee, interim analyses, or stopping rules.

### Dissemination

The study protocol has been registered, and is available on the Chinese Trial Registry website (registered in ChiCTR.org with the identifier ChiCTR-IOR-17013011). The results will be disseminated to all participants, researchers, healthcare providers, and sponsors through study summary documents, courses, presentations, and the Internet. This study will also be published in scientific journals and be presented at conferences to target a wide range of groups.

## Discussion

Compared with conventional exercise styles (e.g., resistance exercise, muscular endurance exercise, and aerobic exercise), Baduanjin typically involves a mind–body integration practice to balance the Yin and Yang in the body and promote blood circulation and Qi for maximizing both physical and mental well-being [37]. Previous studies have shown that regular Baduanjin exercise is beneficial in improving psychological and physiological outcomes among elderly adults and various clinical populations (e.g., Parkinson’s disease, chronic neck pain, chronic fatigue syndrome-like illness, psychological illness) [38–40]. As a typical mind–body exercise with characteristics of traditional Chinese medicine, Baduanjin may be considered to be an effective exercise for a wide range of populations (e.g., a healthy population or patients with chronic diseases; young, middle-aged, or elderly adults) in promoting health. In recent years, the effect of Baduanjin in health promotion has gradually been accepted by young adults, especially college students in China. An increasing number of studies have found that regular practice of Baduanjin can modulate sub-health [41], improve the body physique and mental health [42, 43], promote sleep quality [44], and motivate Qi circulation [45] in college students. In our previous trial, we found that 12 weeks of regular Baduanjin training could improve the lower limb proprioception and flexibility in college students [33]. In this trial, we will observe the effect of 12 weeks of Baduanjin training on the health-related physical fitness of college students. A rigorous study design with randomized allocation and blinding to assessors and statistical analyzers will be applied to reduce bias. It is expected that this trial will create reliable results.

There are some potential limitations to this study. First, it is difficult to monitor the additional physical activity of participants during the study duration. Although all participants will be required to record their daily physical activity or exercise information by using a step counter in their phone, this is not accurate enough to measure their daily activity intensity. Second, due to unexpected accidents such as training time conflicts with other commitments and bad weather, individual adherence to the Baduanjin exercise regimen in the Baduanjin exercise group may be another issue which can impact the study results. Furthermore, blinding of participants is impossible in this trial, because of the nature of the exercise intervention. However, we will make every effort to ensure that outcome assessors, data managers, and statisticians are unaware of the treatment allocations.

Altogether, the results of this trial may provide evidence of whether regular Baduanjin training can improve the health-related physical fitness of college students in China.

